## Abstract

**Background:**

Oxygen therapy is a widely used intervention in acutely ill patients in the intensive care unit (ICU). It is established that not only hypoxia, but also prolonged hyperoxia is associated with poor patient-centered outcomes. Nevertheless, a fundamental knowledge gap remains regarding optimal oxygenation for critically ill patients. In this randomized clinical trial, we aim to compare ventilation that uses conservative oxygenation targets with ventilation that uses conventional oxygen targets with respect to mortality in ICU patients.

**Methods:**

The “Conservat*I*ve versus *CON*ventional oxygenation targets in *I*ntensive *C*are patients” trial (ICONIC) is an investigator-initiated, international, multicenter, randomized clinical two-arm trial in ventilated adult ICU patients. The ICONIC trial will run in multiple ICUs in The Netherlands and Italy to enroll 1512 ventilated patients. ICU patients with an expected mechanical ventilation time of more than 24 h are randomized to a ventilation strategy that uses conservative (PaO_2_ 55–80 mmHg (7.3–10.7 kPa)) or conventional (PaO_2_ 110–150 mmHg (14.7–20 kPa)) oxygenation targets. The primary endpoint is 28-day mortality. Secondary endpoints are ventilator-free days at day 28, ICU mortality, in-hospital mortality, 90-day mortality, ICU- and hospital length of stay, ischemic events, quality of life, and patient opinion of research and consent in the emergency setting.

**Discussion:**

The ICONIC trial is expected to provide evidence on the effects of conservative versus conventional oxygenation targets in the ICU population. This study may guide targeted oxygen therapy in the future.

**Trial registration:**

Trialregister.nl NTR7376. Registered on 20 July, 2018.

## Introduction

### Background and rationale {6a}

Arterial oxygenation may be influenced by different factors, including lung function, lung mechanics, ventilator settings, hemodynamics, and the amount of oxygen administered. The risks of hypoxia are well-established, and prolonged exposure to severe hyperoxia has also been shown to induce lung injury [1–4]. In two meta-analyses, arterial hyperoxia and liberal use of oxygen therapy were associated with hospital mortality and poor functional outcome in various subsets of critically ill patients [5, 6]. However, the retrospective nature of the meta-analyzed studies hamper general acceptance of lower target ranges and supraphysiological oxygenation is still frequently pursued in order to avoid hypoxemia. In a Dutch study, the nadir for unadjusted mortality was retrospectively determined at oxygenation levels of 110–150 mmHg [7], but pilot data suggest that more conservative oxygenation targets may also be safe and even improve clinical outcomes [8].

Accordingly, a fundamental knowledge gap regarding optimal oxygenation has been recognized in international literature [9–15].

In a randomized clinical trial on optimal oxygenation in ICU patients that was published in 2016, improved survival was demonstrated in patients who received oxygen according to the conservative strategy (PaO_2_ targeting 70–100 mmHg or arterial oxyhemoglobin saturation (SpO_2_) targeting 94–98%) in comparison to a conventional control group (PaO_2_ up to 150 mmHg or SpO_2_ targeting 97–100%) [16]. This trial was the first randomized clinical study to demonstrate a potential harm of liberal oxygen administration, which earlier had been suggested by observational and preclinical studies [17–21].

However, after this first RCT, three comparable trials have been completed that did not support the previous findings that favored lower oxygenation targets [22–24]. Thus, uncertainty still exists on optimal oxygenation targets in ICU patients.

### Objectives {7}

As a replication study, we have set up a multicenter trial comparing conservative and conventional oxygenation targets in ICU patients, to confirm findings from a previous study that showed improved survival in ICU patients treated with lower oxygenation targets [16]. To that end, we applied similar in- and exclusion criteria and similar oxygenation targets.

### Trial design {8}

The ICONIC study is an investigator-initiated, multicenter, international, open-label, parallel, 1:1 randomized clinical two-arm equivalence trial in mechanically ventilated ICU patients.

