### Outcomes {12}

The primary endpoint is all-cause mortality at 28 days after randomization. The secondary study endpoints are as follows:
The number of ventilator-free days and alive at day 28, defined as the number of calendar days from day 1 to day 28, the patient is alive and breathes without assistance of the mechanical ventilator. Ventilator-free days are according to the definitions by the Dutch National Intensive Care Evaluation (NICE) registry [27].ICU length of stay (LOS)Hospital LOSICU mortalityHospital mortality90-day mortalityIschemic events (cardiac, neurological and peripheral)

Follow-up (in participating subjects from the Netherlands):
Quality of life at 6 and 12 monthsPatient opinion of research and consent in the emergency setting at 6 months after randomization

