### Sample size {14}

Based on an expected mortality in the control group of 24% (source: Dutch NICE foundation; NICE online [27]), we will include 1512 patients to detect an absolute difference in mortality of 6% (2-sided, alpha 0.05, power 80%, similar allocation of subjects to each group and corrected for 4% dropouts). The choice of 6% was motivated by the difference of 8% found in a previous trial [16] comparing conventional to conservative oxygenation targets and what could be considered clinically acceptable.

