## Statistical methods

### Statistical methods for primary and secondary outcomes {20a}

#### Primary outcome

The primary endpoint, all-cause mortality at day 28, is analyzed using Kaplan Meier. The statistical analysis will be based on the intention-to-treat principle, with patients analyzed according to their assigned treatment arms, except for cases withdrawn or without informed consent. The primary outcome will be assessed using a two-sided superiority hypothesis test, with a significance level of 0.05 and presented with two-sided 95% confidence intervals. In addition, we will perform a per-protocol analysis to check for robustness of results. The per-protocol group analysis only considers patients of the conservative group if 50% or more of the PaO_2_s in the blood gas analysis is equal to or below 10.7 kPa (80 mmHg), and patients of the conventional group if 50% or more of the PaO_2_ in the blood gas analysis is equal to or above 14.7 kPa (110 mmHg).

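### The design section labels the trial an equivalence trial, while its aim, sample size and primary test are all for superiority and no equivalence margin is given

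*Protocol article*

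**What the plan says.** The Trial design section states the framework as a "parallel, 1:1 randomized clinical two-arm equivalence trial in mechanically ventilated ICU patients".

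The other sections that bear on the primary comparison describe a search for a difference:

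- **Objectives.** The trial is a replication, intended "to confirm findings from a previous study that showed improved survival in ICU patients treated with lower oxygenation targets".
- **Outcomes.** "The primary endpoint is all-cause mortality at 28 days after randomization".
- **Sample size.** "Based on an expected mortality in the control group of 24"%, "we will include 1512 patients to detect an absolute difference in mortality of 6" percentage points, with the settings "2-sided, alpha 0.05, power 80%, similar allocation of subjects to each group and corrected for 4% dropouts". On the size of the effect: "The choice of 6% was motivated by the difference of 8% found in a previous trial", together with a remark about clinical acceptability.
- **Primary outcome (Statistical methods).** "The primary outcome will be assessed using a two-sided superiority hypothesis test, with a significance level of 0.05". Two-sided 95% confidence intervals are to accompany it, and a per-protocol analysis serves as a robustness check.
- **Discussion.** The question is again whether outcomes differ between the two targets.

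The article states no equivalence margin, no pair of one-sided tests, and no rule that the confidence interval must lie inside a margin.

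**The concern.** Equivalence and superiority trials have reversed hypotheses. In a superiority trial the null is no difference, and failing to reject it leaves the question open. In an equivalence trial the null is a difference at least as large as a stated margin, and rejecting it is a positive finding that the arms are alike. One primary comparison cannot be both.

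The stake is how a null result is read. That outcome is realistic here, since the Background section reports three comparable trials that did not support the earlier benefit. With equivalence in the published design statement, a non-significant superiority test could be presented as the conclusion the trial was designed to reach. The design does not support that conclusion.

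**Working it through.** **Inputs.** From the Sample size section: control mortality 24%, difference to detect 6 points, two-sided alpha 0.05, power 80%, equal allocation, 4% dropout, total 1512. Evaluable per arm: 1512 × 0.96 / 2 = 725.76, about 726.

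**1. Which design does 1512 belong to?** For two proportions with pooled variance under the null:

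n per arm = [1.960 √(2 × 0.21 × 0.79) + 0.842 √(0.24 × 0.76 + 0.18 × 0.82)]² / 0.06² = 723 (rounded up).

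Total 2 × 723 = 1446, and 1446 / 0.96 gives 1507, within 1% of 1512. The unpooled formula gives 1500 after dropout. A continuity correction gives 1512 before dropout and 1575 after it. At 726 per arm, the power for 24% versus 18% is 80.2%. The figure is therefore an ordinary two-sided superiority size for a reduction. For a rise from 24% to 30%, the same method needs 1790.

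**2. What would equivalence need?** The article gives no margin, so one must be assumed. With two one-sided tests, 24% mortality in both arms and a true difference of zero:

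n per arm = 2 × 0.24 × 0.76 × (z₁₋ₐ + 1.282)² / m²

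where a is the one-sided level, m the margin, and 1.282 the normal quantile for 80% power. At m = 6 points this gives 868 per arm for a = 0.05 (1736 / 0.96 = 1809 in total) and 1065 per arm for a = 0.025 (2130 / 0.96 = 2219 in total). Neither is close to 1512.

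**3. How precise will the trial be?** SE = √(2 × 0.24 × 0.76 / 726) = 0.0224.

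- 95% CI half-width: 1.96 × 0.0224 = 4.4 points.
- 90% CI half-width: 1.645 × 0.0224 = 3.7 points.
- A just non-significant result, with an observed difference of about 4.4 points, has a 95% CI from about 0 to 8.8 points. That passes the 6 points the trial is sized to detect.

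**4. How often is a real difference missed?**

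| True mortality versus 24% | Chance of a non-significant result |
|---|---|
| 20% (4-point fall) | 55% |
| 18% (6-point fall) | 20% |
| 30% (6-point rise) | 27% |

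**5. Power to show equivalence at the planned size, arms truly identical.** Power = 2Φ(m / SE − z) − 1, set to 0 when negative. For m = 6 points: 0.06 / 0.0224 = 2.68. Then 2Φ(2.68 − 1.96) − 1 = 0.53, and 2Φ(2.68 − 1.645) − 1 = 0.70.

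| Assumed margin | 95% CI rule | 90% CI rule |
|---|---|---|
| 4 points | 0% | 11% |
| 5 points | 21% | 44% |
| 6 points | 53% | 70% |
| 8 points | 89% | 95% |

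At 4 points the 95% rule can hardly succeed, because the half-width (4.4) exceeds the margin.

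**6. The gap between non-significant and equivalent.** At an assumed 6-point margin, equivalence needs an observed difference below 6 − 4.4 = 1.6 points (95% CI) or 6 − 3.7 = 2.3 points (90% CI). Superiority is already non-significant below about 4.4 points. Results between these limits are non-significant without showing equivalence.

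**The case against.** The strongest reply is that this is one stray word. The objective, the sample size, the named test and the Discussion all point to superiority, and the abstract describes a two-arm trial without the equivalence label. The Primary outcome section governs the inference and is unambiguous. A 95% CI is already planned, so much of the safeguard against misreading is in place. This largely stands, and it is why the sample size and the analysis need no change. It does not remove the contradiction, because the wrong word sits in the section whose purpose is to declare the framework. Nor is this detail left to an analysis plan: a separate plan could add a margin, but it could not make two published sections agree.

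Four stronger readings are tempting, and the article does not support them:

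- **A null result will be reported as equivalence.** No section says so, and there is no equivalence rule to invoke. The label makes that presentation possible; it does not commit the trial to it.
- **Superiority is the only test in the plan.** It is the confirmatory test of the primary endpoint. Secondary endpoints, the per-protocol analysis and the safety monitoring have their own comparisons.
- **The 6 points are an equivalence margin in disguise.** The remark on clinical acceptability might suggest this, but the 6 points are used as the difference to detect and are motivated by the 8% seen in the earlier trial. A loosely worded minimal important difference is an equally good reading.
- **The trial is underpowered for its stated purpose.** The stated 80% is power to detect a difference, and it reproduces. The equivalence powers above depend on assumed margins, and at 8 points the planned size would be ample.

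**Conclusion.** The design label is wrong as written. It contradicts the objective, the sample size and the primary-endpoint test, and no margin or decision rule supports it. The sample size and the test themselves are correct for superiority.

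The practical consequence is confined to the reading of a non-significant result. The figures that need no margin are the 4.4-point half-width, the interval reaching 8.8 points, and the 20% or 27% chance of missing a true 6-point difference. They rest on 24% control mortality, 726 evaluable patients per arm and the normal approximation. The equivalence powers additionally rest on a margin that the article does not give, so they should be read as a range (0% to 89% with a 95% CI, 11% to 95% with a 90% CI, for margins of 4 to 8 points) and not as a property of the plan.

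**What to change.** In the Trial design section, replace the word equivalence with superiority. In the Primary outcome section, add one sentence: a non-significant result will be interpreted through the risk difference in 28-day mortality and its 95% CI, and will not be described as equivalence.

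The cost is wording only. The sample size, test, alpha, endpoint and conduct are unchanged. What is given up is an equivalence claim that the plan does not specify.

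If the sponsor does intend equivalence, the change is no longer editorial. The plan would then need a justified margin, a confidence-interval rule, a sample size or honest power to match, and a defined role for the per-protocol analysis. Either way, the matter should be settled before results are known.

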### Eligibility criteria {10}

#### Inclusion criteria

In order to be eligible to participate in this study, a subject must meet all of the following criteria:
Age ≥ 18 yearsAdmission to an ICU participating in this studyNeed for intubation and mechanical ventilationExpected mechanical ventilation time of 24 h or longerInclusion within 2 h after start of invasive ventilation in the ICU or if previously intubated and ventilated within 2 h after admission to the ICU

#### Exclusion criteria

A potential subject who meets any of the following criteria will be excluded from participation in this study:
Readmission to the ICU within the same hospital admissionPrior ICONIC study inclusionInvasive ventilation longer than 12 h directly preceding admissionDecision to withhold life-sustaining treatment at the time of inclusionAcute respiratory distress syndrome (ARDS) with a PaO_2_/FiO_2_ ratio less than 150 mmHgAcute decompensation of chronic obstructive pulmonary disease (COPD) and chronic hypoxemiaUse of home oxygen therapySevere not rapidly reversible low cardiac output shock (for example: cardiac index ≤ 2 L/min/m^2^)Documented severe pulmonary hypertensionVeno-arterial extracorporeal membrane oxygenation (VA-ECMO)Underlying disease indication for hyperoxygenation (for example: carbon monoxide intoxication, decompression sickness, gas embolism)Severe anemia (hemoglobin < 4.0 mmol/l) that is not rapidly reversible (e.g., if blood transfusions are not possible or not allowed for religious reasons)Uncontrollable intracranial hypertensionParticipation in other interventional trials which could influence ICONIC study intervention and/or endpointsSuspected or confirmed pregnancy

### Who will take informed consent? {26a}

Informed consent will be obtained according to local legal regulations. Informed consent will be obtained, if possible, prior to start of intervention. However, due to the emergency setting of this trial, this will occur in the minority of subjects. For the majority of subjects, inclusion will take place in an emergency setting when the patient is incapacitated and deferred consent from a proxy will be obtained as soon as possible. Information about the trial will be given by the treating physician to the proxy. After deferred proxy consent is obtained, decisional capacity of the participant will be assessed frequently and when regained during the ICU stay deferred subject consent must be obtained.

If the patient dies before informed consent or deferred (proxy or subject) consent is obtained, the study data will be used. The Dutch central committee of research in humans (Centrale Commissie Mensgeboden Onderzoek (CCMO)) states that legal representation of a patient ends after death and that therefore the obligation to obtain signed consent no longer applies after death of the patient [25].

### Additional consent provisions for collection and use of participant data and biological specimens {26b}

This trial does not involve collecting biological specimens for storage.

## Interventions

### Explanation for the choice of comparators {6b}

The comparators were chosen based upon previously found oxygenation targets associated with greater survival in ICU patients [8, 26] and to have sufficient contrast in PaO_2_ between the two randomization groups.

### Intervention description {11a}

In patients randomized to the “conservative-targets” arm, oxygenation will be targeted at PaO_2_ 55–80 mmHg (7.3–10.7 kPa). Because PaO_2_ is not continuously measured, oxygenation targets can be steered on SpO_2_ in between PaO_2_ measurements. Corresponding SpO_2_ to conservative PaO_2_ targets needs to be determined per individual patient (usually approximately 91–94%).

Patients randomized to the “conventional-targets” arm, oxygenation will be targeted at PaO_2_ between 110 and 150 mmHg (14.7–20 kPa). Corresponding SpO_2_ to conventional PaO_2_ targets will also be determined per individual patient (usually approximately 96–100%).

#### Invasive ventilation

The allowed ventilation modes are volume-controlled ventilation, pressure-controlled ventilation, pressure support ventilation, closed loop ventilation, and combined modes. Furthermore, INTELLiVENT-ASV (Hamilton Medical AG, Bonaduz, Switzerland) is allowed with the automatic oxygenation (FiO_2_ and PEEP) adjustment turned off.

The inspired oxygen fraction (FiO_2_) and positive end-expiratory pressure (PEEP) values are determined and titrated by means of the pre-specified and randomly assigned oxygenation targets. The respiratory rate is adjusted to maintain a blood pH of 7.20 to 7.45. In case of metabolic acidosis or alkalosis, a lower or higher than normal PaCO_2_ can be accepted, left to the discretion of the attending physician. The lowest level of PEEP is 5 cmH_2_O; recommended FiO_2_–PEEP combinations are provided in Table 1. Deviation from the table is allowed in individual patients when indicated and is left to the discretion of the attending physician. Recruitment maneuvers are allowed, when deemed necessary by the attending physician.

**Table 1 Tab1:** Recommended combinations of FiO_2_ and PEEP. Deviation from the table is allowed in individual patients when indicated and is left to the discretion of the attending physician

FiO_**2**_	PEEP (cmH_**2**_O)
0.21	5
0.30	5
0.40	5
0.40	8
0.50	8
0.50	10
0.60	10
0.70	10
0.70	12
0.70	14
0.80	14
0.90	16
0.90	18
1.00	18
1.00	20
1.00	22
1.00	24

In both arms, tidal volume is titrated per predicted bodyweight (PBW), which is calculated according to a previously used formula: 50 + 0.91 × (centimeters of height − 152.4) for males and 45.5 + 0.91 × (centimeters of height − 152.4) for females. Tidal volumes are targeted at 6–8 ml/kg PBW.

#### Weaning

Daily assessment of the ability to breathe with pressure support ventilation is required as soon as FiO_2_ ≤ 0.4 or when the PEEP level and FiO_2_ level are lower than the day before.

In addition, the ventilator can be switched to pressure support ventilation at any moment if the attending nurse or physician considers the patient awake enough to breathe with pressure support ventilation. Assessment of the ability to breathe with pressure support is also required in case patient–ventilator asynchrony is noticed (ineffective breathing; double triggering, use of accessory respiratory muscles). A patient is assumed to be ready for extubation when the following criteria are met for at least 30 min, and the final decision for extubation is made by the attending physician:
Responsive and cooperativeAdequate cough reflexPaO_2_/FiO_2_ of > 200 mmHg with FiO_2_ ≤ 40%Respiratory rate of 8 to 30 per minuteNo signs of respiratory distress (i.e., marked accessory muscle use, abdominal paradox, diaphoresis, marked dyspnea)Pressure support level < 8 cmH_2_OHemodynamically stable (systolic blood pressure 80 to 160 mmHg and heart rate 40 to 130/min) and no uncontrolled arrhythmiaTemperature > 36.0 and < 38.5 °C

If a patient is able to breathe without assistance but subsequently requires additional ventilation within 28 days after randomization, the same oxygenation target protocol is resumed.

#### After invasive ventilation

When a patient is extubated, the PaO_2_ targets should still be pursued within the type of oxygen support for which the patient has a medical indication. High-flow nasal oxygen or non-invasive ventilation should not be started solely for the ICONIC study PaO_2_ targets, because this could influence duration of ICU admission. If this means the PaO_2_ targets are not achieved after extubation, this should be accepted. The following rules apply:
For patients randomized to the conventional oxygenation target: always give a nasal cannula with 5 L of oxygen, except if PaO_2_ > 150 mmHg (> 20 kPa).For patients randomized to the conservative target: preferably no oxygen therapy, except if PaO_2_ < 55 mmHg (< 7.3 kPa).

### Criteria for discontinuing or modifying allocated interventions {11b}

Subjects can leave the study at any time for any reason if they wish to do so without any consequences. The investigator can decide to withdraw a subject from the study for urgent medical reasons. When deferred consent is not obtained after randomization and provisional inclusion of a patient or when a patient withdraws consent. The replacement of the randomization subject will be done in the automated randomization scheme.

To avoid prolonged exposure to very high inspiratory oxygen concentrations, the allocated intervention can temporarily be modified in the conventional PaO_2_ target group when FiO_2_ is above 80% for more than 2 h and/or PEEP is above 15 cmH_2_O for more than 2 h. In order to provide guidance when clinicians are in a situation with high inspiratory oxygen concentrations, we created a flowchart (Fig. 1).

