## Assignment of interventions: allocation

### Sequence generation {16a}

Randomization sequence is generated by a dedicated computer randomization software program (Castor EDC, Amsterdam, The Netherlands) using variable block sizes and is stratified per participating center.

Details of blocking are provided in a separate document that is unavailable to those who enroll participants or assign interventions.

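### Patients withdrawn for medical reasons can drop out of the primary mortality analysis; secondly, the protocol does not say whether 1512 counts randomised or retained patients

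*Protocol article*

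**What the plan says.** All references are to the Protocol article.

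- **Medical exit.** Criteria for discontinuing or modifying allocated interventions {11b}: "The investigator can decide to withdraw a subject from the study for urgent medical reasons". The section does not say what happens to outcome collection afterwards. It separately allows a temporary change of target, described only for the conventional group and triggered by high FiO2 or PEEP.
- **Analysis set.** Statistical methods for primary and secondary outcomes {20a}: patients are analysed as assigned, but withdrawn cases and cases lacking consent are taken out.
- **Blinding.** Who will be blinded {17a}: clinicians and outcome assessors know the allocation; only the data analysts do not.
- **Missing data.** Sections {18b} and {20c}: complete-case analysis, with multiple imputation as a sensitivity analysis only if more than 5% of primary outcomes are missing. Little or no loss is expected.
- **Replacement.** Section {11b}, directly after an unfinished sentence about deferred consent not obtained or consent withdrawn: "The replacement of the randomization subject will be done in the automated randomization scheme".
- **Sample size.** Section {14}: a total of 1512, "similar allocation of subjects to each group and corrected for 4% dropouts".

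**The concern.** Intention-to-treat protects the comparison because nobody leaves it for a reason that arises after randomisation. Sections {11b} and {20a} together open such a route. A clinician who knows the arm judges that a patient should come out for a pressing medical reason, the patient is recorded as withdrawn, and the withdrawn case is then left out of the primary analysis. These patients are likely to be sicker than average, and the reason for leaving may be connected with the assigned target. If exits differ between arms in number or prognosis, the mortality difference is biased. Neither replacement nor a dropout allowance corrects this, since both restore numbers and not comparability.

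A second, smaller matter is that losses through consent appear to be handled in two places: by replacement in {11b} and, possibly, by the 4% allowance in {14}. There is no cap on replacement, and it is not stated whether 1512 is the number randomised or the number kept.

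**Working it through.** **1. Reproducing the plan's own total.** Inputs from {14}: control mortality 24%, difference 6 points (so 18%), two-sided alpha 0.05, power 80%, equal arms, 4% dropout.

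- n per arm = [1.960·√(2·0.21·0.79) + 0.842·√(0.24·0.76 + 0.18·0.82)]² / 0.06² = 723 (rounded up), so 1446 in total.
- With 4% dropout: 1446/0.96 = 1507, close to 1512.
- Conversely, 1512 × 0.96 = 1452 analysed (726 per arm), with power 80.2%.

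So 1512 fits its stated inputs with the 4% included. A continuity-corrected formula gives exactly 1512 before any dropout (756 per arm). Had that been used, the 4% would not be inside the total, but the protocol says that it is.

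**2. Tracing a medical withdrawal through the text.**

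- {11b}: the exit is from the study, not merely from the target.
- {20a}: withdrawn cases are excluded from the intention-to-treat analysis.
- {17a}: the person deciding is not blinded.
- {18b} and {20c}: the imputation safeguard starts only above 5% missing. Fifteen exits among 1452 are 15/1452 = 1.0%, so it would not be triggered, and excluded cases might not be counted as missing at all.

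**3. Size, under assumed inputs.** The protocol gives no rate of medical withdrawal and no mortality for such patients. Assume that about 2% of the conservative arm leave (15 of 726), none of the conventional arm, and that those who leave have 40% or 50% mortality. Expected deaths in the full arm: 0.18 × 726 = 130.7.

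- At 50% mortality: (130.7 − 7.5)/(726 − 15) = 123.2/711 = 17.3%, a shift of 0.7 point.
- At 40% mortality: (130.7 − 6)/711 = 124.7/711 = 17.5%, a shift of 0.5 point.

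For scale, the standard error of the difference is √[(0.24·0.76 + 0.18·0.82)/726] = 2.1 points, so the shift is roughly a fifth to a third of a standard error. In this illustration it favours the conservative arm. Exits from the other arm would push the other way, and similar exits in both arms would largely cancel.

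**4. What 1512 counts.** If patients are replaced until 1512 are retained, the number randomised is 1512/(1 − w), where w is the proportion replaced. If 1512 is the number randomised and nobody is replaced, power falls with w. Apart from 4%, the values of w are assumptions.

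| w | Randomised to retain 1512 | Power if 1512 randomised, none replaced |
|---|---|---|
| 4% | 1575 | 80.2% |
| 10% | 1680 | 77.6% |
| 15% | 1779 | 75.2% |
| 20% | 1890 | 72.7% |

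**The case against.** The best defence of {20a} is grammatical. Its exclusion can be read as covering consent only, either withdrawn or never given. Patients withdrawn for medical reasons would then stay in the analysis. That reading is possible, but {11b} uses withdrawal for the investigator's medical decision too, and nothing in {20a} limits the term to consent.

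It is also fair to say that the medical exit is permissive and may be rare. {18b} expects almost no loss for the primary outcome, and {26a} keeps the data of patients who die before consent. Patients who merely miss their target remain in the intention-to-treat analysis, with a per-protocol analysis alongside. This limits the likely size of the problem but does not close the route.

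Several stronger readings are tempting and are not supported:

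- **Follow-up stops after a medical withdrawal.** The article does not say so. What is documented is exclusion from the analysis.
- **The conservative arm will lose more patients.** A temporary modification is described for one arm only, but no text shows that this makes study withdrawal likelier in the other. The 2%-versus-none split above is an illustration.
- **Medically withdrawn patients are replaced.** The replacement sentence follows the consent fragment and attaches most naturally to it.
- **Replacement breaks concealment.** That would need the vacated allocation to be given to the next patient. No text says so, and {16a} describes a computer sequence "using variable block sizes and is stratified per participating center", with block details withheld from those who enrol.
- **1512 is wrong, or the trial is underpowered because of the overlap.** The total reproduces, and replacing patients does not reduce power. The 4% may also be meant for losses other than consent, since dropout is not defined.

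**Conclusion.** The main point holds: read plainly, {11b} and {20a} together permit exclusions from the primary mortality analysis that are decided after randomisation by unblinded clinicians and can depend on treatment and prognosis. The illustrated bias of 0.5 to 0.7 point is modest beside the 6-point target. It rests wholly on assumed withdrawal and mortality rates and on exits confined to one arm. The case for change is that the route is avoidable at almost no cost, not that a large bias has been shown.

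The secondary point is an ambiguity, not an arithmetical error. The protocol does not fix whether 1512 is randomised or retained, or which losses the 4% is meant to absorb.

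**What to change.** **Main change, in {11b} and {20a}.** State that a withdrawal for medical reasons ends neither the collection of 28-day mortality, 90-day mortality and ischaemic events nor membership of the intention-to-treat set. Record the date and reason. Only refusal or withdrawal of consent ends the use of data. When, and in which arm, the allocated target may be modified is a clinical matter for the sponsor to reconcile within {11b}; no rule is proposed here.

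**Secondary change, in {11b} and {14}.** Complete the unfinished sentence so that it is clear who is replaced. State whether 1512 counts randomised or retained patients and which losses the 4% covers. Dropping replacement altogether is a trade-off, not an obvious improvement. Most patients enter under deferred consent ({26a}), and if loss reached an assumed 10% without replacement, power would fall to 77.6%.

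**Cost.** A few sentences in an amendment, one eCRF field, and a little more follow-up.
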